SENSe therapists will not be blinded due to pragmatic reasons. It is planned that each therapist will deliver SENSe therapy to up to 12 stroke survivors. A secondary analysis will permit investigation of the association between stroke survivor outcomes achieved and the therapist’s amount of experience in delivering SENSe therapy. The study is approved by Austin Human Research Ethics Committee (HREC/18/Austin/153), and all experiments will be performed in accordance with the Declaration of Helsinki. Site-specific ethics approvals were also obtained. All participants will give voluntary informed consent.

Sample size: Stroke survivors—The SENSe CONNECT study design requires a within-subject, repeated measures analysis. The within-group analysis from the original SENSe randomized controlled trial (RCT) revealed a Cohen d of 0.366 for the somatosensory function outcome (repeated measures, small group *n* = 22/50; [34]). To achieve a within-group effect of d = 0.366 for a power of 0.8, a minimum sample of *n* = 61 is required. In the current study, the proposed sample size of *n* = 72 to 192 (i.e., 18 to 48 deliveries at each of the 4 centers) achieves this minimum and allows for dropout or poor recruitment. Assuming the variability in changes found in the SENSe RCT is replicated in the delivery of SENSe therapy, a maximum sample size of *n* = 192 will have a high degree of precision for estimating the effect size obtained within the SENSe therapy centers. The larger sample size will also facilitate generalizability of effect estimates to the broader target population of survivors of stroke living in the community. Therapists—At each specialist SENSe therapy center, it is planned that 3 or 4 therapists will each deliver SENSe therapy to 6 to 12 stroke survivors (i.e., 18 to 48 deliveries at each site; 72 to 192 across sites). A sample of 12 to 16 therapists was chosen to maximize replication across upskilled therapists while exploring the association between the amount of experience in delivery of SENSe therapy and therapy outcomes.

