### 2.2. Participants

Participants for the SENSe CONNECT study include both therapists and stroke survivors.

Therapists: Inclusion criteria—Qualified occupational therapist or physiotherapist; current registration to practice; and willing to participate in the upskilling in SENSe therapy, undertake evaluation, and actively participate in mentoring and treatment fidelity activities to develop competency to deliver SENSe therapy. There are no additional exclusion criteria for the participants who are therapists. Replacement therapists will be recruited as needed. As a pragmatic implementation trial, restrictions will not be imposed on therapist participants’ experience or number of stroke survivors treated. However, demographic information for all therapist participants will be collected to ascertain relationships between stroke survivor outcomes and therapist characteristics.

Stroke survivors: People with stroke living in the community and presenting with new or chronic somatosensory impairment will be recruited. Stroke survivors may be referred via partner organizations, neurologists, rehabilitation physicians, general practitioners, other organizations, or self-referral. Inclusion criteria: A clinical diagnosis of stroke (including infarct or hemorrhage, people with a second stroke, no restriction on time since stroke); impaired touch sensation, limb position sense, and/or tactile object recognition of the upper limb, identified clinically and with screening tests; medically stable; able to give informed consent; able to comprehend simple instructions; willing to commit time to participate in the SENSe therapy program; and living in the community. Key exclusion criteria: Sensory impairment not due to stroke; severe unilateral spatial neglect (measured via line bisection and shape cancellation task); prior history of other central nervous system dysfunction with an unstable or progressive prognosis; severe to moderate cognitive impairment (i.e., not able to comprehend simple instructions or sustain attention needed to participate in treatment); not able to give informed consent; physical limitations that prevent participation in therapy tasks (e.g., contracture of the hand, or unhealed wounds); and unable to participate in a clinical appointment lasting 30 min. Thus, the design tests effectiveness with relatively unselected survivors of stroke in the community.

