Therapists: Treatment fidelity is a primary outcome for therapists and will be assessed as the ability to deliver SENSe therapy with high fidelity measured with a criterion-based checklist (comprising 29 components core to the delivery of SENSe therapy; 80% fidelity) and customized documentation audit checklist [43]. Fidelity will be assessed by an independent person, using a document audit, for each therapist after delivery of each 6-week program of SENSe therapy. In addition, a sample of treatment sessions (early, middle, and late in the sequence of 10 sessions for the stroke participant) will be observed and rated by an independent person using a session-based treatment fidelity checklist. Therapist participants will also be assessed for change in practice behaviors related to SENSe therapy (secondary outcome), specifically change in knowledge, skill, and confidence levels. These outcomes will be assessed using pre–post implementation questionnaires [12] adapted for the SENSe CONNECT study. The pre-questionnaire will be completed prior to upskilling, credentialing, and first delivery of SENSe therapy. The post-implementation questionnaire will be completed after delivery of therapy to the 12th stroke survivor treated, or following the last scheduled delivery of therapy, for that therapist.

Therapist experience effect: Therapist experience will be measured according to the number of completed deliveries of the SENSe therapy program, with delivery of 7 or more sessions per stroke survivor the criterion for a completed delivery. Each therapist is anticipated to deliver SENSe therapy to 6 to 12 survivors of stroke.

Resource utilization and therapy costs: Resources used by survivors of stroke will be collected at all assessment occasions for the usual care wait list and intervention periods using a patient/carer survey. Resources will be assigned prices to convert these into costs using contemporaneous Australian reference sources. Costs will be inflated/deflated for a common reference year (e.g., 2022) using the Total Health Price Index [53], as required. Program level costs of intervention delivery: SENSe therapy costs will include the cost of upskilling therapists, equipment, and delivering the intervention according to the model of care established, as well as determining the cost of usual care. The type and quantity of each resource used will be collected in natural units, e.g., number of sessions and time taken to train therapists.

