Effect of SENSe therapy: We will evaluate the therapeutic gain in arm somatosensory function for stroke survivors (primary outcome) during the SENSe therapy phase compared to that of the usual care phase by estimating the mean within-person difference between the two trends and the associated 95% confidence intervals. The magnitude of change in arm somatosensory function under the two conditions will be calculated as a standardized effect size and compared to the benchmark effect size obtained in the original SENSe RCT (comparable cohort) [34]. Statistical estimates of change will be reported with 95% confidence intervals, and the extent of overlap across studies in these estimates of change will be described. Confidence intervals for the difference between mean change scores from the present and benchmarked study [34] will also be obtained. The analysis design will include the SENSe therapy center as a variable, to evaluate its potential systematic effect. Individual participant characteristics that may impact magnitude of therapeutic gain, such as age and time post-stroke, will be explored. Improvement in secondary outcomes, i.e., clinician-rated performance in valued activities, arm use, and quality of life, will also be evaluated pre–post therapy. Depending on verification of the normal distribution assumption, either a t-distribution or a bootstrapping method will be used to obtain the confidence interval. Maintenance of the intervention effect will be evaluated at the 12-week follow up (A4).

Treatment fidelity and behavior change: High fidelity delivery will be defined as a score of 80% or higher on the SENSe treatment fidelity checklists [43]. Audit data from treatment sessions will be independently summarized for each SENSe therapy treatment program delivered. The number of therapy deliveries achieving high treatment fidelity will be summarized. Pre- and post-implementation questionnaires of therapist knowledge, confidence, and ability to deliver SENSe therapy will be summarized and response tendencies will be examined using contingency tables, McNemar’s test, and graphical representation.

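### McNemar's test is the only inferential test named for therapist knowledge, skill and confidence; if the items are graded, it has low power for small to moderate change in 12 to 16 therapists

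*Protocol article*

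**What the plan says.** Section 2.4 (Outcomes, Therapists) defines a therapist outcome of "change in practice behaviors related to SENSe therapy (secondary outcome), specifically change in knowledge, skill, and confidence levels". On the instrument it says: "These outcomes will be assessed using pre–post implementation questionnaires [12] adapted for the SENSe CONNECT study". The first questionnaire comes before upskilling. The second follows the twelfth stroke survivor treated or the therapist's last scheduled delivery.

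Section 2.8 (Treatment fidelity and behavior change) plans a summary of the responses and adds that "response tendencies will be examined using contingency tables, McNemar’s test, and graphical representation". No other test, and no interval for the size of change, is named for this outcome.

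On numbers, section 2.1.2 says: "A sample of 12 to 16 therapists was chosen to maximize replication across upskilled therapists". The other reason given there is exploration of the experience effect. Section 2.2 adds: "Replacement therapists will be recruited as needed". The article gives no response format, no cut-point and no power target for the questionnaires.

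**The concern.** McNemar's test compares two paired binary responses. A graded answer has to be reduced to two classes first. After that, only therapists who change class carry information. A move from the lowest grade to the middle one counts for nothing if both lie below the cut, and the result can depend on where the cut is placed.

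With 12 to 16 pairs there is little information to spare. The study tests a knowledge-transfer intervention, and therapist knowledge, skill and confidence are direct measures of its effect. A non-significant McNemar result after a moderate real gain could be misread as no change.

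**Working it through.** **1. The article's own power figure.** The only formal calculation is for stroke survivors (2.1.2): "To achieve a within-group effect of d = 0.366 for a power of 0.8, a minimum sample of *n* = 61 is required". A paired t-test with d = 0.366, power 0.80 and two-sided alpha 0.05 (assumed, as alpha is not stated) gives 60.5, so 61. The figure reproduces, but it does not cover the therapist questionnaires.

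**2. Smallest significant result, exact McNemar.** Let b and c be the numbers moving up and down, and m = b + c. The two-sided p-value is 2 × Σ C(m, k) / 2^m, summed over k = 0 to min(b, c).

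- 5–0: 2 × 1/32 = 0.0625
- 6–0: 2 × 1/64 = 0.031
- 7–1: 2 × (1 + 8)/256 = 0.070
- 8–1: 2 × (1 + 9)/512 = 0.039

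So at least six therapists must cross the cut, and six suffice only if all go one way. Six is 6/12 = 50% or 6/16 = 37.5% of the therapists. If one worsens, eight must improve. This step assumes nothing about the response scale.

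**3. Power of exact McNemar by share of therapists crossing the cut.** If nobody worsens, power is P(B ≥ 6) with B ~ Binomial(n, share improving). If some worsen, it is the multinomial probability of all significant (b, c) pairs. The shares are assumptions.

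| Improve / worsen | n = 12 | n = 16 |
|---|---|---|
| 30% / 5% | 8% | 20% |
| 40% / 5% | 23% | 42% |
| 50% / 5% | 42% | 64% |
| 60% / 5% | 61% | 81% |
| 40% / 0% | 34% | 67% |
| 50% / 0% | 61% | 90% |
| 60% / 0% | 84% | 98% |

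For 80% power, 58% (n = 12) or 45% (n = 16) must improve if nobody worsens, and 73% or 60% if 5% worsen.

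**4. What the cut costs if the item is graded.** Assumptions: a five-level item from a latent normal variable, thresholds at −1, 0, 0.7 and 1.5 SD, pre–post correlation 0.5, and a cut at the top two levels (24% there before training). Each cell rests on 3,000 simulated studies, two-sided 5% level.

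| Latent shift | McNemar, n = 12 | Signed-rank, n = 12 | McNemar, n = 16 | Signed-rank, n = 16 |
|---|---|---|---|---|
| 0.5 SD | 4% | 21% | 9% | 35% |
| 0.8 SD | 14% | 56% | 29% | 72% |
| 1.0 SD | 26% | 75% | 53% | 91% |
| 1.5 SD | 70% | 98% | 90% | 100% |
| 2.0 SD | 91% | 100% | 99% | 100% |

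Both tests are in exact form. Repeat simulations under the same kind of assumptions move these values by a few percentage points; the ranges given in the conclusion allow for that.

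Most of the gain comes from keeping the levels. A plain sign test on the five levels, which uses only the direction of each change, gives 18%, 47% and 65% (n = 12) and 28%, 60% and 82% (n = 16) at shifts of 0.5, 0.8 and 1.0 SD.

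**The case against.** The strongest reply is that the questionnaire is not shown. The response format sits in the cited instrument, and nothing in the article excludes that the items tested are yes/no, for which McNemar's test is suitable. That stands, and it makes the point conditional.

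A reader might infer that the plan throws the graded information away. The article does not support that. Summaries, contingency tables and graphs stand beside McNemar's test, and all can show every response level. Only the named inference would lose the detail.

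A reader might also infer that the study can hardly detect any change in therapists. That is too strong. With 60% improving and none worsening, exact power is 84% (n = 12) to 98% (n = 16), and under the five-level model a 1.5 SD shift is found with 70% to 90% power. Large gains are plausible, because the first questionnaire precedes about 13 to 16 hours of training.

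Other versions of the test are less conservative. At n = 12 with 50% improving and none worsening, mid-p gives 81% and the asymptotic version 93%, against 61% exact. The asymptotic version is unreliable with so few discordant pairs, and every version ignores change within a class. Leaving the version to an analysis plan is not a fault.

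Finally, the outcome is secondary, fidelity is the therapists' primary outcome, and the article makes no power claim here. Replacement therapists could also raise the number of pairs. These points limit the importance of the matter; they do not make McNemar's test the better choice for graded items.

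**Conclusion.** The point holds as a minor, conditional inefficiency. It is not an error in a stated figure or a contradiction. If the items are graded, the one inferential test named has low power for small to moderate change. For shifts of 0.5 to 1.0 SD, exact McNemar gives about 3–28% (n = 12) and 8–53% (n = 16), against about 19–75% and 31–91% for the exact signed-rank test.

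These figures rest on an assumed five-level item, a top-two cut, a pre–post correlation of 0.5 and the exact form of McNemar's test. The need for six discordant therapists, all in one direction, rests only on the exact test at the two-sided 5% level.

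**What to change.** In section 2.8, or in the analysis plan, state that graded items and total scores will be compared before and after with an exact paired ordinal test (Wilcoxon signed-rank), and that the median or mean paired change will be reported with a 95% CI. Keep McNemar's test, in exact or mid-p form, for items that are truly yes/no. If a graded item is still to be dichotomised, fix the cut-point before the data are seen. Keep the planned summaries, tables and graphs.

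The cost is about one sentence of analysis wording. No new data, visits or therapists are needed.

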#### 2.1.2. Specialist SENSe Therapy Centers and SENSe CONNECT Protocol

Four specialist SENSe therapy centers have been set up to deliver SENSe therapy to stroke survivors across three states in Australia. The new specialist therapy centers are linked with healthcare networks and universities or research institutes. The SENSe therapy centers will permit delivery of therapy to stroke survivors living in the community. Therapy may be delivered at the center or in the client’s home.

Occupational therapists and physiotherapists skilled and credentialled in SENSe therapy will deliver SENSe therapy to stroke survivors across the specialist therapy centers, using a pragmatic, within-subject wait list design [42]. The wait list design will evaluate change in outcomes over a 6-week period of usual care not associated with SENSe therapy, compared to a 6-week period of SENSe therapy delivered by credentialled therapists. During the wait list phase, participants will receive usual care, which will be monitored. Upper-limb therapy will not be restricted for participants during the control wait list phase; rather, participants will receive ‘usual care’ conditions [44]. Consistent with an independent review and analysis of ‘usual care’ usually received in health services in Australia (based on national audit and knowledge-translation study), this will usually not involve specific sensory rehabilitation, such as SENSe therapy [44]. Participants may continue to receive usual care during the SENSe therapy intervention period. Our prior controlled clinical trials provide evidence that exposure to sensory stimuli alone and/or current usual care is not usually sufficient to affect clinically significant improvement in somatosensory function [34,36,37]. All services and usual care received will be monitored.

Stroke survivors attending specialist SENSe therapy centers will be assessed on four occasions: baseline (i.e., Assessment 1, A1); after 6 weeks of usual care (i.e., A2); after 6 weeks of SENSe therapy (i.e., A3); and at follow up, 12 weeks post A3 (i.e., A4). All participants attending SENSe therapy centers will receive SENSe therapy (10 sessions) over a 6-week period. Assessors for health outcomes of stroke survivors will be blinded to study design and timing of therapy delivery. Researchers and statisticians involved in the data analysis will also be blinded to study design and timing of therapy delivery.

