### 2.4. Outcomes

Access to evidence-based sensory rehabilitation: The primary outcome is the number of complete deliveries of SENSe therapy at the SENSe therapy center by therapists credentialled in SENSe therapy. A delivery will be counted as complete if it meets the criterion of at least 7 sessions delivered with a stroke survivor.

Stroke survivors: The primary outcome is change in arm somatosensory function, pre–post SENSe therapy, across three somatosensory domains, measured using standardized, quantitative somatosensory measures and a normalized summary impairment index calibrated to normed age-matched performance [34,45]. The index will be derived from scores on the Tactile Discrimination Test [46], Wrist Position Sense Test [47], and functional Tactile Object Recognition Test [48]. Each of these quantitative measures assesses the person’s ability to discriminate different somatosensations; i.e., texture discrimination, wrist joint proprioception, and haptic object recognition of the upper limb. Comparable ranges of impairment from just noticeable to extreme impairment defined for each measure enable the normalization of the three test scales for comparison in clinical and research settings [45].

The following secondary outcomes will also be assessed: client-rated performance and satisfaction of valued activities, using the Canadian Occupational Performance Measure (COPM) [49] and clinician-rated performance on the same valued activities using the Performance Quality Rating Scale for Somatosensation after Stroke [50]; arm use, using Motor Activity Log-14 [51]; and health-related quality of life, using the Assessment of Quality of Life (AQoL-6D) [52]. See Table 1 for the schedule of study outcomes.

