Therapist experience effect: The availability of 6 to 12 sequential cases treated with SENSe therapy by each of the 12 to 16 therapists will allow exploration of the hypothesis that a trend towards better outcomes arises with experience of therapy delivery. Individual therapeutic gain scores will be adjusted for initial sensory impairment, consistent with our prior analysis of which individual variables affect therapeutic gain [57]. Growth curve models will be explored for the sequence of adjusted therapeutic gains from each of the therapists (*n* = 12–16) to evaluate the autocorrelation structure of residuals and the viability of a common model. A pooled estimate of the effect of treatment experience will then be obtained via a meta-analysis, or hierarchical linear modelling if a common trajectory form is applicable.

Economic evaluation: We will report a cost description analysis for usual care and the SENSe therapy interventions and summarize these data as part of a cost consequence analysis [58] presenting the disaggregated costs and primary and secondary outcomes for stroke participants. The incremental cost-effectiveness of SENSe therapy compared to monitored wait list usual care will also be evaluated as the cost per achievement of improved arm somatosensory function (primary outcome for stroke survivor). We will also use simulation modelling to estimate the incremental cost per Quality Adjusted Life Year gained with SENSe therapy, drawing data from the study and the published RCT for SENSe [34]. One-way sensitivity and multivariable uncertainty analyses will be performed to assess the robustness of results. The findings from the economic evaluation will be used to inform business cases for future adoption of SENSe within the Australian healthcare context and may have relevance to other countries with similar funding models for healthcare. Results will be reported according to the Consolidated Health Economic Evaluation Reporting Standards (CHEERS) [59,60].

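### The therapist-experience trend is modelled on gain scores adjusted for a single initial impairment score; using both pre-therapy scores as covariates is at least as precise and costs almost nothing

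*Protocol article*

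**What the plan says.** Section 2.8 (Therapist experience effect) sets out a sequence of steps. First: "Individual therapeutic gain scores will be adjusted for initial sensory impairment". Then: "Growth curve models will be explored for the sequence of adjusted therapeutic gains from each of the therapists". Finally: "A pooled estimate of the effect of treatment experience will then be obtained via a meta-analysis, or hierarchical linear modelling" (the latter if a common trajectory form applies). The aim is exploratory: the data "will allow exploration of the hypothesis that a trend towards better outcomes arises with experience of therapy delivery".

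The article describes gain in two ways. Section 2.4 says: "The primary outcome is change in arm somatosensory function, pre–post SENSe therapy", which is A3 − A2. In section 2.8 (Effect of SENSe therapy) the target of the main analysis is "therapeutic gain in arm somatosensory function for stroke survivors (primary outcome) during the SENSe therapy phase compared to that of the usual care phase". There, each person's change in the usual-care phase is subtracted from that person's change in the therapy phase, which gives (A3 − A2) − (A2 − A1) = A3 − 2·A2 + A1. The experience paragraph does not say which of the two it takes, nor whether the initial score is A1 or A2.

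Section 2.1.2 and Table 1 schedule the somatosensory measures for every stroke survivor at A1, at A2 (end of the usual-care phase, before therapy) and at A3 (end of therapy).

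**The concern.** A1 and A2 are both measured before the therapist treats the case, so the therapist's experience cannot affect them. For comparing one case with the next they are covariates, and their best weights can be estimated. The between-phase difference fixes those weights in advance. It is the right contrast for the mean effect because it removes the usual-care change. As a case-by-case outcome it counts the error in A2 twice and adds the error in A1. Adjusting for one of the two scores repairs only part of this.

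The experience question is a named study aim (section 1, fourth aim), and the planned numbers are limited: 12 to 16 therapists with 6 to 12 cases each. Precision lost through the choice of outcome cannot easily be recovered, and a flat estimated trend could be reported as no experience effect when the analysis was simply too noisy.

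**Working it through.** **The plan's own figure.** The article gives no standard error, power or sample size for the experience trend. Its one such figure, a minimum of 61 for d = 0.366 and power 0.8 (section 2.1.2), concerns the mean effect. It reproduces with a paired t test at an assumed two-sided alpha of 0.05 (power 0.803 at n = 61) and does not bear on this point.

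**Assumptions.** The article gives no visit correlations. I take equal variances (set to 1) at A1, A2 and A3 and a correlation r of 0.7 to 0.9, either equal for all pairs or AR(1). With a common trend and the same cases, the standard error of the trend is proportional to the residual SD, so ratios of residual SDs are ratios of standard errors.

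**Residual variances, equal correlations, with values at r = 0.8**

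- Reference, A3 given A1 and A2: (1 − r)(1 + 2r)/(1 + r) = 0.2 × 2.6/1.8 = 0.289
- A3 − 2·A2 + A1 given A1: (1 − r)(5 + r) = 0.2 × 5.8 = 1.16
- A3 − 2·A2 + A1 given A2: 2(1 − r)(1 + 2r) = 2 × 0.2 × 2.6 = 1.04
- A3 − A2 given A1: 2(1 − r) = 0.40
- A3 − A2 given A2: (1 − r)(1 + r) = 0.36

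For example, √(1.16/0.289) = 2.00 and √(0.36/0.289) = 1.12.

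**AR(1).** The reference is 1 − r². The variance ratios to it, in the same order, are 5 − 4r + r², 2, 2 − 2r + r², and 1.

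**Standard error relative to A3 on A1 and A2**

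| Gain, adjusted for | Equal r = 0.7 / 0.8 / 0.9 | AR(1) r = 0.7 / 0.8 / 0.9 |
|---|---|---|
| A3 − 2·A2 + A1, A1 | 2.01 / 2.00 / 2.00 | 1.64 / 1.56 / 1.49 |
| A3 − 2·A2 + A1, A2 | 1.84 / 1.90 / 1.95 | 1.41 / 1.41 / 1.41 |
| A3 − A2, A1 | 1.19 / 1.18 / 1.16 | 1.04 / 1.02 / 1.00 |
| A3 − A2, A2 | 1.10 / 1.12 / 1.14 | 1.00 / 1.00 / 1.00 |
| Either gain, A1 and A2 | 1.00 | 1.00 |

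The last row is an identity: once A1 and A2 are both covariates, subtracting multiples of them from the outcome leaves the trend estimate unchanged.

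**Simulation check** (equal r = 0.8, between-phase gain adjusted for A1 against the reference). With 16 therapists × 12 cases the standard errors were 0.0223 and 0.0113; with 12 × 6 they were 0.0729 and 0.0360. For the same gain and covariate at 16 × 12, adjusting in a separate step gave 0.0223 and adjusting within the model gave 0.0224. The separate step is therefore not the source of the loss.

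**Conditions that shrink the ratio.** If therapists' slopes vary (assumed SD 0.05 per case), the simulated 2.0 falls to 1.53 (16 × 12) or 1.82 (12 × 6). If A1 and A2 correlate at 0.8 to 0.9 but A3 correlates with them at only 0.6 to 0.8, the between-phase ratio is 1.24 to 1.75 and the A3 − A2 ratio 1.02 to 1.14.

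**Illustration in power.** Assume 14 therapists × 9 cases, equal r = 0.8 and a trend of 0.04 SD per case. The within-therapist sum of squares of case number is 14 × 60 = 840, so SE = √(variance)/√840, and approximate power is Φ(0.04/SE − 1.96).

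- A3 on A1 and A2: SE 0.0185, power about 58%
- A3 − A2 given A2: SE 0.0207, power about 49%
- Between-phase gain given A1: SE 0.0372, power about 19%

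**The case against.** The strongest reply is that the article does not commit to the costly version. In section 2.8 each phase can be read as having its own gain, with the difference between trends named separately, and section 2.4 defines the outcome as pre–post therapy change. On that reading gain is A3 − A2. Adjusted for A2, it is already an analysis of covariance with the A2 weight estimated from the data. Adding A1 then gains 10 to 14% in standard error under equal correlations and nothing under AR(1). The analysis is also labelled exploratory, no precision is claimed for it, and a fuller plan may define both gain and the initial score.

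Much of this stands. It limits the size of the loss and its consequence. It does not show that a gain adjusted for one score is ever preferable: in no case examined was it more precise than using both scores. The choice of an adjusted gain as outcome is stated in the article, not left open.

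A reader might go further and infer any of the following, which the documents do not support:

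- *The plan doubles the standard error.* That needs the between-phase gain, adjustment for a single pre-therapy score and near-equal correlations. The article fixes neither the gain nor the score.
- *Adjusting before modelling is the fault.* The simulation shows no loss from that step.
- *The plan's trend is biased by drifting case mix and the alternative is not.* The article gives no drift. With an assumed drift of 0.1 SD per case and a true slope of 0.03, the proposed model returned 0.041, while A3 − A2 given A1 returned 0.027. The alternative is not immune.
- *The same loss affects the center, age and time-post-stroke analyses.* No loss has been shown for those.

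**Conclusion.** The point holds as a modest, nearly free improvement in precision. Under equal variances and visit correlations of 0.7 to 0.9 (equal or AR(1)), the stated outcome inflates the standard error of the experience trend by about 1.4 to 2.0 times if gain is the between-phase difference. If gain is A3 − A2, the inflation is about 0 to 19%, and it is zero when A3 − A2 is adjusted for A2 under AR(1). If the initial score were taken to mean A1 and A2 together, the loss would vanish under either definition. The cause is the fixed weight on A2 together with the omission of one pre-therapy score. All correlations here are assumptions. Because the analysis is secondary and exploratory, what is at risk is an uninformative answer to the fourth aim; the study's main result is not affected.

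**What to change.** Replace the adjusted-gain step in section 2.8 with wording such as: *The experience effect will be estimated in one hierarchical model with the A3 somatosensory index as outcome, the A1 and A2 indices as covariates, case number within therapist, and therapist random effects.* Using A3 − A2 as the outcome with the same two covariates is equivalent and keeps the language of gain. State that the between-phase difference is used for the mean effect only.

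The cost is a change of wording and one further covariate degree of freedom. No new data are needed, since all three scores are already scheduled for every participant, and hierarchical modelling is already among the planned options.
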